### Strategies to assess and improve adherence to interventions {11c}

User adherence in mHealth interventions varied based on user-related, content-related, and technology (personalise remainders, user-friendly, technically stable App, personal support, and gamification features) related barriers and facilitators of engagement [41, 42]. The intervention group [LvL UP] will receive notifications and reminders about the coaching session’s date and time, daily random lifehack, and motivational messages to engage with the LvL UP App. Additionally, a dashboard link to monitor the participant’s live activity regarding last-time interaction, tools used, and the current level is considered to reach up to support adherence with the participants. Thus, the following three strategies will be implemented: calling participants who have not interacted for 2 weeks with the LvL UP App after baseline; texting the participants who have low interaction (e.g. using the App once/twice for 2 weeks), and sending automatic SMS 3, 5 and 7 weeks after the baseline visit to encourage them to use the App.

The HAPPY App will detect the number of logged entries and the last interaction with the app. A manual schedule reminder will be sent by the App if the participant has not read the suggested articles or documents.

### Relevant concomitant care permitted or prohibited during the trial {11d}

The participants will be excluded if they have enrolled in a concurrent lifestyle intervention research study during the study. However, trial participants can receive concomitant treatment (e.g. psychotherapy, pharmacology), which will be assessed during the follow-up period.

### Provisions for post-trial care {30}

Access to the Happy App will continue for the 3-year follow-up period after the trial for all the participants.

### Outcomes {12}

Table 1 shows the outcomes and timeline of the study. The primary outcome will be the onset of T2D/confirmed by a 2-h 75 g oral glucose tolerance test (OGTT) over a 4-year study period. OGTT will be done at the screening visit, year 1 visit, and follow-up visits in years 2, 3, and 4. Secondary outcomes include (a) onset of impaired fasting glucose and impaired glucose tolerance; (b) changes in cardiometabolic variables (body weight, HbA_1c_, insulin, blood lipids, blood pressure), and (c) changes in women’s body composition as assessed by bioelectrical impedance analysis (BIA). Secondary measures will be taken at baseline visits, middle point, year 1, and 2, 3, and 4-year follow-up period.

**Table 1 Tab1:** Outcomes and timeline

Assessments	Screening visit	Baseline visit	Midpoint visit (26/27 weeks)	Year 1 visit	Year 2 visit (follow-up)	Year 3 visit (follow-up)	Year 4 visit (follow-up) endpoint
Lab tests							
OGTT test	X				X	X	X
Height, weight and blood pressure measurements	X	X	X	X	X	X	X
Bio-sample collection: buccal swab, saliva, and stool samples		X		X			X
BIA		X		X	X	X	X
Fasting blood draw		X	X	X	X	X	X
Questionnaires							
Demographics	X			X			
GDM and family history of diabetes	X						
Spouse and child health	X			X			
Lifestyle and dietary	X			X			
Diabetes awareness	X			X			
14-day e-Diary recording		X	X	X	X	X	X
SF-36		X	X	X	X	X	X
STAI		X	X	X	X	X	X
BDI-II		X	X	X	X	X	X
CERQ		X	X	X	X	X	X
MEQ		X	X	X	X	X	X
PSQI		X	X	X	X	X	X
SHS		X	X	X	X	X	X
HLQ		X	X	X	X	X	X
PSS-4		X	X	X	X	X	X
WHO-5		X	X	X	X	X	X
Child-related questionnaires							
BISQ-R-SF		X		X			
CSHQ		X		X			
StimQ toddler/preschool		X		X	X	X	X
ASQ-3		X		X	X	X	X
BRIEF-2		X		X	X	X	X
BASC-3-BESS Parent Form		X		X	X	X	X
Questionnaires administrated within the LvLUP App (intervention group only)							
PHQ-4		x	x				
IPAQ-SF		x	x				
MFFQ		x	x				

*OGTT* 2-h 75 g oral glucose tolerance test, *BIA* Bioelectrical impedance analysis, *SF-36* short-form health survey, *STAI* The Stare-Trait Anxiety Inventory, *BDI-II* Beck Depression Inventory, *CERQ* Cognitive Emotion Regulation Questionnaire, *MEQ* Morningness-Eveningness Questionnaire, *PSQI* The Pittsburgh Sleep Quality Index, *SHS* Subjective Happiness Scale, *HLQ* Health Literacy Questionnaire, PSS-4 Perceived Stress Scale 4, *WHO-5* World Health Organization Wellbeing Index, *BISQ-R-SF* Brief Infant Sleep Questionnaire-Revised Short Form, *CSHQ* Children’s Sleep Habits Questionnaire, StimQ toddler/preschool Cognitive Home Environment Questionnaire, *ASQ-3* Ages & Stages Questionnaires-3, *BRIEF-2* Behaviour Rating Inventory of Execute Functions-2, *BASC-3-BESS Parent Form* Behavioral and Emotional Screening System, *PHQ-4* Patient Health Questionnaire, *IPAQ-SF* The International Physical Activity Questionnaire-Short Form, *MFFQ* Modified Food Frequency Questionnaire

Additionally, we will assess changes in women’s mental well-being by completing the following questionnaires at all study visits:

*Beck Depression Inventory* (BDI-II): A 21-item self-reported rating inventory using a 3-point Likert scale that measures symptoms and severity of depression, classified as follows: minimal (0–13); mild (14–19); moderate (20–28); and severe (29–63). The BDI-II internal consistency as measured by Cronbach’s alpha ranges from 0.87 to 0.93 [43].

*State-Trait Anxiety Inventory* (STAI): A 40-item self-report questionnaire using a 4-point Likert scale. The STAI measures two types of anxiety — state anxiety and trait anxiety, which are classified as no or low anxiety (20–37), moderate anxiety (38–44), and high anxiety (45–80). Internal consistency coefficients for the scale have ranged from 0.86 to 0.95 [44].

*Cognitive Emotion Regulation Questionnaire* (*CERQ*): A 36-item self-report measure designed to identify the cognitive emotion regulation strategies (or cognitive coping strategies) someone uses after having experienced adverse events or situations. It is commonly used to assess individual differences in the cognitive regulation of emotions in response to stressful, threatening, or traumatic life events. Internal consistency ranges from 0.72 and 0.83 [45].

*Subjective Happiness Scale (SHS):* A 4-item self-report measure to assess an individual’s overall happiness. Internal consistency ranges from 0.79 to 0.94 [46].

*WHO-5 Wellbeing* Index (*WHO-5*): A 5-item self-reported questionnaire that aims to assess mental wellbeing over the last 2 weeks. The WHO-5 shows reliability across countries between 0.86 and 0.96 [47].

*Perceived Stress Scale* (*PSS-4*): A brief self-report measure of the extent to which recent life events are considered stressful. The PSS-4 has demonstrated acceptable criterion validity and internal consistency (*α* = 0.72) [48].

*The short Form Health Survey* (*SF-36*): Indicates overall health status; it aims to assess the impact of clinical and social interventions on quality of life in several domains. The SF-36 has shown a reliability of 0.90 [49].

*Health Literacy Questionnaire* (*HLQ*): The HLQ examines an individual’s understanding, access and engagement with health information and health services. The HLQ Cronbach’s alpha has shown an internal consistency of 0.87 [50].

Moreover, changes in women’s sleep will be assessed using the following measurements:

*Morningness-Eveningness Questionnaire* (*MEQ*): A 19-item MEQ aims to assess morningness and eveningness where questions are asked preferentially, i.e. asking respondents to indicate when, for example, they would prefer to wake up or start sleep, rather than when they do. MEQ internal consistency is 0.82 [51].

*Pittsburgh Sleep Quality Index* (*PSQI*): Measures the quality and patterns of sleep-in adults. It differentiates “poor” from “good” sleep quality by measuring seven areas (components): subjective sleep quality, sleep latency, sleep duration, habitual sleep efficiency, sleep disturbances, use of sleeping medications, and daytime dysfunction over the last month. The PSQI Cronbach’s alpha has shown good internal consistency ranging from 0.64 to 0.83 [52].

Furthermore, changes in the health and well-being of the women’s children will be collected. Only children born during a GDM pregnancy will be considered in this study. The following measurements will be used:

*Cognitive Home Environment Questionnaire* (*StimQ*): The StimQ-toddler (age 12–35 months)/StimQ-pre-school (for age 36 – 72 months) is designed to identify the different types of toys and games that children have in the home and the kinds of activities that mother and child do together [53]. The StimQ has demonstrated good internal and external reliability (*α* = 0.85) [54].

*Ages & Stages Questionnaires-3* (*ASQ-3*) (1–66 months): The ASQ-3 development screening tool assesses children’s communication, autonomy, compliance, adaptive functioning, affect, and interaction with people. ASQ-3 is a reliable and valid instrument with a test–retest reliability of 92%, a sensitivity of 87.4% and a specificity of 95.7% [55].

*Behaviour Rating Inventory of Executive Functions-2 (BRIEF-2) parent form*: BRIEF-2 is designed for use in medical and educational settings to estimate the global executive function of children/youth and determine whether a comprehensive assessment is appropriate (age 5–18 years). BRIEF-2 has shown reliability coefficients ranging between 0.8 and 0.9 [56].

*Behavioural and Emotional Screening System (BASC-3-BESS) Parent Form*: This screens children and adolescents’ behavioural and emotional strengths and weaknesses (age 3–18 years 11 months). BASC-3 BESS has high internal consistency at 0.80 [57].

Changes in the child’s sleep will be assessed at the baseline visit and the first-year visit. The following is a description of child sleep questionnaires:

*The Brief Infant Sleep Questionnaire-Revised Short Form* (*BISQ-R-SF*): A parent-reported toddler (0–3 years) sleep over the prior 1 week, assessing sleep patterns, ecology, and parental perceptions of sleep. The BISQ-R indicates excellent reliability at 0.80 [58].

*Children’s Sleep Habits Questionnaire (CSHQ) Short Form (SF)version*: The SF-CSHQ assesses the frequency of children’s behaviours associated with common paediatric sleep difficulties for children between 48 and 72 months. The SF-CSHQ has been validated, showing Internal consistency coefficients ranging from 0.90 to 0.94 [59].

After completing the 1-year RCT period, both groups will be followed up for 3 years. During the follow-up visits, body measurements, OGTT, bio-sampling, and data collection will be conducted, and the questionnaires listed above.

Additionally, the intervention group will also complete the following questionnaires through the LvL UP App:

*Patient Health Questionnaire-4* (*PHQ-4*): A 4-item self-report measure that assesses anxiety and depression symptoms. Each item is scored on a 4-point scale (0–3), and scores range from 0 to 27. The score can be used to describe a patient’s symptoms in one of the five categories: none (0–2), mild (3–5), moderate (6–8), and severe (9–12), The PHQ-4 has been shown to have good internal reliability (Cronbach alpha = 0.82) [38].

*Modified Food Frequency Questionnaire* (*MFFQ*): A 7-item self-report checklist of food and beverages with a frequency response section based on My Healthy Plate Singapore[60].

*The International Physical Activity Questionnaire-Short Form* (*IPAQ-SF*): A self-report measure assesses the type of intensity of physical activity and sitting time[39]. The IPAQ-SF has shown a moderate internal consistency of 0.647 [61, 62].

#### Screening survey overview and follow-up

The screening surveys will include questions of 8 types: (i) socio-demographics, (ii) GDM and family history of diabetes, (iii) medical history, (iv) lifestyle, (v) dietary, (vi) diabetes awareness, (vii) paternal demographics and health and (viii) child demographics and health (see Table 2). Those surveys will also be completed in baseline and 1-year visits (see Table 1).

**Table 2 Tab2:** Screens survey variables overview

(i) *Socio-demographics*: Age, ethnicity, marital status, highest level education, nationality, residency status, occupation, number of children, accommodation type, total monthly household income
(ii) *GDM and family history of diabetes*: First diagnosis of GDM, last diagnosis of GDM, total of GDM diagnosis, number of births, number of babies, mode of delivery, preterm delivery, insulin during pregnancy, medication during pregnancy, medication to treat GDM, maternal complications, neonatal complications, breastfeeding
(iii) *Medical history*: Past and current medical conditions or surgeries, paternal medical history, maternal medical history, siblings’ medical history
(iv) *Lifestyle*: What is considered a healthy lifestyle, barriers to achieving a healthier lifestyle, coping strategies during stress, following specific diet(s), reasons for choosing the diet(s), alcohol consumption, tobacco consumption, eating habits, physical activity, sleep patterns, stress level, changes in lifestyle in the past 3 months, planning to make changes in any lifestyle behaviours in the future, use of activity tracking wearable, use of lifestyle mobile interventions, currently joining a fitness or wellness program
(v) *Dietary*: Dietary habits, oil/fat used for cooking, consumption of coffee/tea or other beverages, rice, fish, red meat, pork, chicken, salt, soya, and vegetables
(vi) *Diabetes awareness*: knowledge about diabetes, GDM, its causes and risks, last time checked blood sugar level, HbA1c test, fasting, 2-h OGTT
(vii) *Paternal demographics and health*: Age, ethnicity, highest level of education, nationality, residency status, occupation, overall height, overall weight, paternal medical history, maternal medical history, siblings’ medical history
(viii) *Child demographics and health*: Age, ethnicity, sex, weight at birth, height at birth, head circumference, education level, medical condition(s), preterm birth, hospitalizations

### Participants timeline {13}

The participants’ flow for the trial is outlined in Fig. 1. Once participants are identified through one of the recruiting methods, they will be invited to the SICS clinic for screening, in which a consent form will be explained and signed, and OGTT test, height, weight, blood pressure measures, HbA1c (finger proc test) and sociodemographic survey will be completed. Those who are eligible will be randomised to one of the two arms (comparison or intervention group) and will subsequently be asked to take follow-up height, weight and blood pressure measurements, BIA, report the child’s height and weight, fasting blood draw, collection of the buccal swab, saliva, and stool sample, and complete questionnaires for the mother and their child at midpoint (26/27 weeks) visit, and year one visit after randomisation. After the midpoint assessments, additional interventions will be delivered via the HAPPY App to subjects in the intervention group who require further recommendations to improve their BMI or manage their body weight. During the 3 year-followed-up periods, participants will be asked to complete the following: (a) OGTT test; (b) height, weight and blood pressure measurements; (c) BIA; (d) fasting blood draw; (e) collection of the buccal swab, saliva and stool samples; (f) reported child’s height and weight; (g) complete mother and child questionnaires; (h) issue of Oura Ring (8 weeks); and (i) 14-day e-Diary recording in year 2, 3 and 4 visit. The schedule of enrolment, intervention, and assessments for the trial is outlined in Fig. 2.

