### Trial design {8}

This study is a 1-year randomised controlled trial (RCT) with 3 years of follow-up. We will conduct a two-arm single parallel assignment individually randomised equal allocation control trial on *n* = 400 women with a history of GDM. It will compare the aggregate effects of the Intervention group (receiving a holistic lifestyle mHealth intervention (LvLUP App), Sleep tracker, Oura ring/Oura App and psychoeducation to promote healthy lifestyle (Happy App)) and (comparison group (Happy App (psychoeducation only), Oura ring and Oura App) at 26/27 weeks, and 1-year visit. After completing the 1-year RCT period, both groups will be followed up in years 2, 3, and 4. We hypothesise that the intervention will reduce the risk of T2D/pre-diabetes and CMDs in post-GDM women.

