## Interventions

### Explanation for choice of comparators {6b}

mHealth may provide practical and scalable support to women adopting and maintaining a healthy lifestyle. The effectiveness of mHealth interventions targeting lifestyle behaviours has been demonstrated [31, 34, 37]. More recently, studies have supported that prevention and promotion request more than one pillar, meaning that holistic lifestyle behaviours, such as PA, diet, sleep, and mental well-being, are more effective in parallel [34]. Studies have shown that education alone is insufficient to support individuals in changing their lifestyles, and it is important to incorporate techniques and behavioural strategies that facilitate and measure the effectiveness of the interventions [31, 34, 37]. Therefore, we propose to compare two mHealth interventions, the intervention group (LvL UP App, Happy App, and Oura Ring) and the comparison group (HAPPY App and Oura Ring). The LvL UP App is based on evidence-based strategies and interactive tools developed in Singapore [35]. The HAPPY App is available to every eligible participant (both groups) in the trial; it provides public holistic health recommendations and displays participants’ health data measured during study visits over time. Also, the Oura ring is a sleep tracker that includes heart rate variability, and a step tracker will be provided to both groups.

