### Intervention description {11a}

The comparison and intervention group will be assigned to holistic lifestyle mHealth interventions. The comparison group (Happy App and Oura ring) will receive only psychoeducation to promote a healthy lifestyle through the HAPPY App and sleep tracking using an Oura ring and associated App. The Happy App was developed by the Singapore Institute for Clinical Sciences (SICS); it encompasses only educational content on lifestyles based on resources from the Singapore Health Promotion Board, including information about diet intake, physical activity, sleep, and mental well-being. The HAPPY app also displays health outcome data collected during the study visits (e.g. body weight, blood pressure, fasting glucose, and 2-h 75 g OGTT). The Oura Ring is an activity-tracking wearable that monitors physical activity, sleep, and heart rate variability, which can be synced with the Oura App.

The intervention group (LvL UP App, Happy App, and Oura Ring) will receive the same Happy App, Oura Ring and Oura App, with the additional LvL UP App version 2.0. The LvL UP App has been developed by the Future Health Technologies Programme at the Singapore ETH-Centre (SEC) for iOS and Android. It is designed to be culturally relevant in Singapore and is based on evidence-based behavioural strategies [35]. A separate paper[35] describes the conceptual model, development process, and characteristics of LvLUP version 1.0. In this study, we will use an updated 2.0. version. The LvL UP App 2.0 is a smartphone-delivered holistic lifestyle intervention focusing on three core pillars: *eat well* (diet), *move more* (PA), and *stress less* (mental well-being), including sleep content in each pillar delivered through a coaching health and tools paradigm.

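### After the midpoint visit the HAPPY App, described as identical in both arms, carries extra BMI and weight interventions for the intervention arm only, so later differences cannot be credited to LvL UP alone

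*Protocol article*

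**What the plan says.** Three sections of the protocol article define the contrast, and they agree with each other.

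- Explanation for choice of comparators {6b} sets LvL UP plus HAPPY plus the Oura ring against HAPPY plus the Oura ring, and adds: "The HAPPY App is available to every eligible participant (both groups) in the trial".
- Intervention description {11a} says of HAPPY that "it encompasses only educational content on lifestyles", and that it also displays participants' own study results. The comparison group "will receive only psychoeducation to promote a healthy lifestyle through the HAPPY App", together with Oura tracking. The intervention group "will receive the same Happy App, Oura Ring and Oura App, with the additional LvL UP App version 2.0".
- Trial design {8} labels HAPPY as psychoeducation and places the trial-period comparisons "at 26/27 weeks, and 1-year visit".

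Participants timeline {13} then adds a component that none of these sections mentions. Once the midpoint visit is done, it says, "additional interventions will be delivered via the HAPPY App to subjects in the intervention group who require further recommendations to improve their BMI". The same sentence extends this to women who need help with weight. Nothing equivalent is stated for the comparison group anywhere in the article.

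**The concern.** The reason for giving both arms the same app and ring is that the arm difference then isolates LvL UP. {6b} relies on this when it argues that education alone is not enough and that behavioural tools must be added. If HAPPY begins to do something different in one arm halfway through the randomised year, it is no longer common background, and the difference between arms is no longer LvL UP alone.

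The add-on is also aimed at things the trial measures. Body weight is a named secondary outcome in Outcomes {12}, beside HbA1c and body composition, and weight is a plausible route to glycaemic outcomes. If an effect grows between the midpoint and year 1, the add-on is a competing explanation. A reader who has seen only {8}, {6b} and {11a} would credit the whole effect to LvL UP.

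**Working it through.** The plan gives no figure on this point to reproduce. The check is a comparison of sections, followed by a count of the results that fall after the add-on starts.

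**1. What each arm receives**

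| | Comparison arm | Intervention arm |
|---|---|---|
| {6b}, {8}, {11a}, whole year | HAPPY (education) + Oura | same HAPPY + Oura + LvL UP 2.0 |
| {13}, to week 26/27 | HAPPY + Oura | HAPPY + Oura + LvL UP 2.0 |
| {13}, after week 26/27 | HAPPY + Oura | HAPPY + Oura + LvL UP 2.0 + additional interventions through HAPPY for women who require them |

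The last row does not fit the first. The firm contradiction is with the statement that HAPPY is the same in both arms and that LvL UP is the addition. The comparison column never changes.

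**2. What falls after the change**

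- Randomised year: 52 − 26 = 26 or 52 − 27 = 25 weeks remain, about half.
- Post-randomisation visits: midpoint and years 1, 2, 3 and 4, so five. Four of the five come after the add-on starts.
- OGTTs: {12} lists screening and years 1 to 4, so all four post-randomisation tests come after it. Table 1, as it reads here, marks only years 2 to 4; that is a separate discrepancy, and then it is three of three. Neither source has an OGTT at the midpoint.
- Follow-up: Provisions for post-trial care {30} keeps HAPPY available to everyone for three more years. No end to the arm-specific material is stated.

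The midpoint contrast in weight and fasting blood measures is therefore free of the add-on. No OGTT-based result is, and that includes the primary outcome.

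**3. Can the size be calculated?**

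The contribution of the add-on to the arm difference in mean weight is (share of the arm receiving it) × (mean effect in recipients). The document gives neither. Purely as assumptions, take a share of 30–50%, an effect of 0.2–2 kg, an SD of weight change of 4 kg and 160–200 women measured per arm:

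- SE of the difference = 4 × √(2/n): 0.447 kg at n = 160 and 0.400 kg at n = 200.
- Lowest: 0.3 × 0.2 = 0.06 kg, or 0.06/0.447 = 0.13 SE.
- Highest: 0.5 × 2 = 1.0 kg, or 1.0/0.400 = 2.5 SE.

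The range runs from negligible to dominant, so the document does not fix the size. The contradiction does not depend on it.

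**The case against.** The best defence is that the trial compares packages. {8} speaks of the aggregate effects of the intervention group, and the statistical section uses the same idea. A component given by a midpoint rule inside the experimental arm is then part of the randomised strategy, and intention-to-treat estimates that strategy against an unchanged comparator. The add-on is disclosed in {13}. It may also be mild: {13} speaks of further recommendations, and {6b} already says HAPPY gives public health recommendations. All of this stands, and it limits the point to attribution and to an inconsistent definition of the package. It does not remove the conflict, because the sections that define the package leave the add-on out and call HAPPY the same in both arms.

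A reader might infer four stronger things that the document does not support.

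- *That the trial's objective cannot be answered from year 1 on.* Randomisation is intact and the package contrast is valid. Only the attribution to LvL UP alone fails.
- *That unblinded staff choose who receives the add-on.* {13} does not say who or what identifies recipients; it could be an automatic rule.
- *That the missing BMI or weight threshold is itself a defect.* A condensed article may leave that to the full protocol.
- *That the false-positive rate is inflated.* If the add-on works, the arms truly differ in weight, and a significant result detects a real package effect.

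Nor is it right that comparison women are left with nothing. They keep HAPPY's health information, the display of their own results and the reading reminders.

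**Conclusion.** The contradiction is real and rests on the article's own words. {13} gives the intervention arm something through HAPPY that {8}, {6b} and {11a} exclude or omit. If {13} is followed, differences at year 1 and later in weight, body composition, HbA1c, impaired fasting glucose or glucose tolerance, and type 2 diabetes measure LvL UP plus the add-on, for the subset of women who receive it. They cannot be attributed to LvL UP alone over the stated comparator. Its reach is four of five post-randomisation visits and every post-randomisation OGTT; its size on any outcome is unknown. The conclusion assumes that {13} means what it says and that no parallel provision for the comparison group exists in the full protocol, which is not shown.

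**What to change.** Reconcile {13} with {8}, {6b} and {11a}. Two versions are consistent:

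1. HAPPY is shared background, as {6b} and {11a} state. Its content, including any BMI-related material, is then the same in both arms, and {13} is corrected to say so.
2. The add-on belongs to the experimental package. Then {8}, {6b} and {11a} name it, and results at year 1 and later are reported as the effect of LvL UP plus the add-on, with the midpoint identified as the only contrast without it.

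In either case, log who received the material and when. Recruitment began in October 2023, so the first women would have reached 26 weeks from about mid-April 2024, and the log may need to be rebuilt for them from app records if those exist. Which clinical content or trigger is appropriate is for the investigators.

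The cost is a protocol clarification and a delivery log or app setting, with no extra visits or participants. Under the second version the claim is slightly narrower.
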